### Secondary measures

Data on demographics, medical history, and diagnoses will be obtained at baseline. Diagnoses will be established using the Structured Clinical Interview for DSM-IV Axis I Disorders (SCID-I) by a well-trained clinical rater. A medical doctor will conduct a full medical examination of each patient and take a thorough medical history. Demographic information and additional clinical information will be collected by a member of the research team.

Data on medications, sleep, menstrual phase, and smoking will be collected at baseline, and after 6 and 12 weeks by a member of the research team. Antipsychotic medications will be indexed by chlorpromazine equivalence. As other medications may impact outcomes, medication use/changes will be tracked using three broad classes: (1) antidepressants, (2) mood stabilizers, and (3) other medications. As indices allowing direct comparisons of medications are not available, for each class, the use of relevant medications at baseline will be documented using a dummy variable (1, 0), along with increases, no change, decreases, or discontinuation at follow-ups (1, 0, − 1, or − 2, respectively). PRN use of medications that may impact cognition (e.g., antihistamines for allergies) during 48 h prior to cognitive and AF tests will be assessed, and the tests will be postponed by 24 h. A similar strategy will be used to handle medications known to impact biomarkers (e.g., SSRIs on BDNF). Sleep during the 24 h prior to cognitive and AF tests will be assessed using an abbreviated version of The Pittsburgh Sleep Quality Index (PSQI), a measure used extensively in SZ studies [61–63]. If a subject reports substantial acute sleep loss that is likely to influence outcomes (< 4 h sleep), the evaluations will be postponed until sleep is restored [64]. Smoking frequency and dependence as well as the number of cigarettes smoked in the 4 h prior to tests (nicotine half-life = ~ 2 h) will be recorded using the Fagerström Test for Nicotine Dependence (FTND) [65–67].

### Psychiatric symptoms

Symptom severity will be assessed with the Positive and Negative Syndrome Scale (PANSS) along with the Beck Depression Inventory (BDI) and Beck Anxiety Inventory (BAI). These assessments will be administered by blinded clinical raters at baseline, 6 weeks, and 12 weeks.

### Cognitive functioning

The composite score of the MATRICS Consensus Cognitive Battery (MCCB) will stand as the primary cognitive functioning assessment and will be administered by blinded clinical raters at baseline, 6 weeks, and 12 weeks. The WTAR will additionally be utilized at baseline to assess reading ability for eligibility.

### Daily functioning

The total score of the Specific Levels of Functioning scale (SLOF; informant version) will serve as the chief daily functioning outcome measure, along with The UCSD Performance-based Skills Assessment (UPSA) and the Schizophrenia Cognition Rating Scale (SCoRS). These measures of daily functioning will be administered by blinded clinical raters at baseline, 6 weeks, and 12 weeks.

### Aerobic fitness

Aerobic fitness will be determined according to participants’ VO_2_max. The VO_2_max tests are completed by an exercise physiologist under the supervision of a physician using electro-magnetically braked cycle ergometers at baseline, 6 weeks, and 12 weeks. A blinded cardiopulmonary physiology expert will review each test to assess for the quality of the test and to ensure that no medical issues arise that would prevent the participant to safely continue exercise.

### Physical activity

Data gathered by an accelerometer (wGT3x-BT) worn on the wrist of the non-dominant hand will provide a measure of objective physical activity [68]. This measure will be performed at the baseline and 12-week follow-up visits. The participant will wear the device for seven consecutive days. Data will be sampled at a frequency of 80 Hz for this duration. Established cut points will be used to determine physical activity [69]. Self-reported physical activity will be assessed with the International Physical Activity Questionnaire [70].

### Biospecimens

A urine sample will be collected by a member of the research team at baseline, 6 weeks, and 12 weeks to be used for toxicology screen (Alere iCup) [71]. Blood samples will be collected by a certified phlebotomist. All samples will be collected between 9 and 10 am to minimize potential diurnal-related variability. The samples will be analyzed for fasting hemoglobin A1c and a lipid panel as well as several biomarkers of cognitive change including neurotrophins and inflammation. Assessment of neurotrophins and inflammation markers will include serum BDNF (R&D Systems, Minneapolis, MN), Nerve Growth Factor - NGF Emax Immuno Assay Systems (Promega, Sunnyvale, CA), Neurotrophin-3 - NT-3 Emax Immuno Assay Systems (Promega, Sunnyvale, CA), Neurotrophin-4 - NT-4 DuoSet ELISA Development Kit (R&D System, Minneapolis, MN), Tumor Necrosis Factor alpha (TNF-α) - MILLIPLEX MAP Human High Sensitivity Immunology Multiplex Assay (Millpore, Billerica, MA), Interleukin-6 (IL6) - MILLIPLEX MAP Human High Sensitivity Immunology Multiplex Assay (Millpore, Billerica, MA), and C-Reactive Protein (CRP) - Cobas Integra 400 Plus (Roche Diagnostics, Indianapolis, IN).

### Emotion regulation, trauma, and quality of life

Questionnaires will be administered by a member of the research team at baseline and 12-week follow-up to collect information regarding emotion regulation (ERQ), alexithymia (TAS-20), childhood trauma (CTQ; only administered at baseline), and the participant’s satisfaction with their life (SWL).

## Safety measurements/adverse events

### Exercise safety measures

At the end of each week of training, potential exercise-related minor and moderate adverse events will be recorded and monitored in addition to serious adverse events (SAE). These may include musculoskeletal/soft tissue (muscle soreness; muscle pull/strain; joint pain, falls), cardiovascular (fatigue; dyspnea; angina or chest pains that are resolved with rest), and skin-related side-effects (blisters; chafing). If chest pain ensues, the medical physician and principal investigator associated with each site will be called to ensure the safety of the participant. Previous reports indicate the risk of adverse events as part of AE-related intervention studies is small [55]. The screening procedure, the use of a “start low and go slow” strategy, the close monitoring of exercise intensity, and the presence of a certified exercise trainer will minimize the risk of SAE and adverse events.

### Suicide risk safety

To address potential safety concerns associated with recruitment of individuals with higher suicide risk, all participants will also be administered a suicide risk assessment (i.e., C-SSRS) by phone at 3 and 9 weeks after baseline, in addition to the suicide risk assessments scheduled during research visits at baseline, 6 weeks, and 12 weeks. All assessments will capture suicidal symptoms from the last administration of the instrument. The raters will consult with the site PI regarding the detection of any suicidality, including passive suicidality. Any subject with a C-SSRS score equal or greater than “4” (Active Suicidal Ideation with Some Intent to Act, without Specific Plan) will require a consultation with [name], the project’s Medical Director, and [name], the project’s suicide expert. Any subject that scores a “5” (Active Suicidal Ideation with Specific Plan and Intent) and judged to be actively suicidal will require urgent clinical evaluation for the possibility of hospitalization, and he/she will be escorted to the closest ER by study staff. [name] has extensive clinical experience treating veterans at high risk for suicide and is available by cell phone 24/7, should clinical consultation regarding study participants be necessary.

### Data monitoring

A NIMH-approved Data and Safety Monitoring Board (DSMB) was established in December of 2017 to oversee the parent study. The members of the DSMB have no financial, scientific, or other conflict of interest with the study and have no affiliations with any of the participating institutions. All materials, discussions, and proceedings of the DSMB are completely confidential and objective. The DSMB will meet every 6 months, or as deemed necessary. Meetings shall be closed to the public because discussions may address confidential patient data. Meetings are attended by the principal investigators and members of his staff. All serious adverse events (SAE) will be reported to the DSMB in addition to the IRB and NIMH.

### Auditing

The current study is monitored by the NIMH Office of Clinical Research (OCR)‘s Clinical Research Education, Support, and Training (CREST) program. (https://www.nimh.nih.gov/funding/clinical-research/nimh-clinical-research-education-support-and-training-crest-program.shtml). The CREST Program aims to establish accurate and verifiable clinical research study data, as well as compliance with Good Clinical Practice and human subjects safety regulations. As part of the program, NIMH staff conduct annual site visits. Additionally, the study is monitored by a Data and Safety Monitoring Board (DSMB) that meets twice annually during the duration of the study.

### Sample size calculations

A power analysis was considered for determining sample size. However, a power analysis was ultimately determined not to be appropriate for the current trial due to the lack of direct data on the relationship between aerobic exercise and reduction in suicide risk. Additionally, recruitment and sample size for this protocol is associated with the ongoing parent R01-funded protocol.

The sample size for the parent R01-funded study is 200 outpatient individuals with SZ. This sample size was determined based on a focus on cognition as the primary outcome, specifically the MCCB total composite score. Prior literature suggests average scores of individuals with SZ fall between 1 and 2.5 standard deviations lower than MCCB averages. Therefore, a 0.50 standard deviation was chosen as a meaningful target effect size for powering the trial. The pilot for the parent study found a large effect size for the AE intervention group compared to controls suggesting a 0.893 standard deviation improvement in the intervention group compared to controls. The parent study sample size calculations assumed a loss-to-follow-up rate of 20% with 80 participants remaining in each arm (100 × 0.8). According to these calculations, the parent study is powered to detect moderate or larger effect size difference with > 80% power. The current study retains confidence that the sample size will provide adequate power to detect a clinically meaningful effect size for suicide risk as the primary outcome.

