**Fig. 1 Fig1:**
[figure not shown]
Detailed study timeline

The interventions and data collection will take place at four geographically diverse sites in the USA: Icahn School of Medicine at Mount Sinai (New York), University of North Carolina at Chapel Hill (North Carolina), Augusta University (Georgia), and Stanford University (California). Each site has access to an exercise facility and spaces dedicated for blood drawing, biological samples analyses and banking, and VO_2_max assessments.

Recruitment of 160 eligible participants will be conducted independently across the four sites. Each site PI will contact clinicians in their healthcare systems and local communities and inform them about the study so that they may inform their eligible patients of the study. Brochures will be left at various relevant outpatient facilities. Interested individuals may speak with a member of the research team who will describe the study in more detail and will invite them to enroll. A short screening interview will be conducted by a researcher remotely by phone to ensure that participants satisfy inclusion criteria.

The number of screens, eligible subjects, and reasons for non-participation will be tracked using the CONSORT guidelines. In an earlier pilot study, a similar procedure was employed with 77% of approached individuals recruited. Refusals were related primarily to logistical/physical health reasons. Subjects’ retention was high, with only 1/16 AE subjects discontinuing due to AE program dislike. In the ongoing parent R01-funded protocol, to date, 71% of approached individuals consented to participate in the study. Formal recruitment for the parent study began in May of 2018. Formal recruitment for this amended study began in November of 2019.

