### Eligibility criteria

Inclusion Criteria: 18–55 years of age; DSM-V diagnoses of SZ, schizoaffective disorder, or schizophreniform disorder; taking an antipsychotic medication for at least 8 weeks and on current dose for 4 weeks and/or taking an injectable depot antipsychotic with no change in last 3 months; medically cleared by a physician to take part in VO_2_max tests and AE/ST training; capacity to understand all the potential risks and benefits of the study; and consented to participate in the parent R01 study (“Improving Cognition via Exercise in Schizophrenia”; MH110623; PIs: [name] & [name]) which aims to assess the impact of AE on cognitive and daily functioning in people with SZ.

Exclusion Criteria: DSM-IV diagnosis of alcohol/substance abuse (except nicotine) within the last month or a diagnosis of alcohol/substance dependence (except nicotine) within the last 6 months; initiation of anti-depressants, mood stabilizers, or other medications known to impact cognition in previous 4 weeks or any changes in doses during this period; history of seizures/head trauma with loss of consciousness (> 10 min) resulting in cognitive sequelae; significant clinical abnormalities in physical examination, lab assessments, or ECG; neurological/medical conditions that could interfere with study participation (e.g., AIDS, unstable cardiac disease, stuttering); BMI ≥ 40; untreated hyper- or hypothyroidism; pregnant/nursing; serious homicidal risk (past 6 months); “moderate” or more severe conceptual disorganization (PANSS ≥ 4); poor English reading ability (WTAR< 7); and participation in a study with cognitive assessment in the past 3 months.

This study has been approved by the institutional review board of the Icahn School of Medicine at Mount Sinai, New York, NY; University of North Carolina, Chapel Hill, NC; Stanford University, Stanford, CA; and Augusta University, Augusta, GA. As part of the informed consent process, the rationale of the study and its methods will be described in detail and all questions will be answered. All participants will be asked to provide written informed consent before participation.

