### Data analyses

All primary analyses will be carried out on an intent-to-treat (ITT) basis, i.e., all subjects randomized will be analyzed according to the treatment they were assigned regardless of adherence to treatment. Level of fidelity to training intensity, accounting for adherence, will be controlled for in these analyses. All statistical tests will be two-sided with critical value α = 5%.

Mixed effects regression will be used to model suicide risk as a function of time (0, 6, 12 weeks), treatment group (AE or ST), interaction of time by treatment group, and site (1, 2, 3, or 4). The efficacy of AE to improve suicide risk in people with SZ will be represented by the statistical significance of the time by treatment group interaction. The effect of AE on mood, sleep, and executive functions will be tested by conducting similar analyses, i.e., mixed effects regression across 0, 6, and 12 weeks.

Mediators in the relationship between AE and suicide risk will be identified by multi-step process. A mediation effect will be estimated by taking the expected value of the total effect of AE on changes in suicide risk and subtracting the effect when changes in mood, sleep, and executive functioning have been controlled. These mediation effects will be tested by fitting a Structural Equation Model (SEM) with change in depressed mood, sleep, and executive function from baseline to 6 weeks as mediators of the relationship between AE treatment and change in suicide risk from baseline to 6 weeks as well as later changes in suicide risk from 6 to 12 weeks using MPlus version 8. The mediator-outcome relationship can be confounded by other time-varying covariates (e.g., BMI changes), and these will also be adjusted for in the model.

Change in suicide risk from baseline will be modeled using mixed effect regression predicted by contemporaneous change in aerobic fitness from baseline as measured by VO_2_max tests (at 6 and 12 weeks), controlling for treatment group and other covariates. The ability of aerobic fitness improvement to predict reduction in suicide risk will be represented by a statistically significant positive regression coefficient for change in aerobic fitness.

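### Adequate power is claimed for suicide risk, but the only supporting calculation is the parent trial's, made for a cognition endpoint and a larger enrolment

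*Protocol article*

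**What the plan says.** The Sample size calculations section makes three statements that need to be read together.

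- For this study, "a power analysis was ultimately determined not to be appropriate for the current trial". The reason given is that there are no direct data linking aerobic exercise to lower suicide risk.
- For the parent trial, which enrols 200 and has the MCCB composite as its primary outcome, "a 0.50 standard deviation was chosen as a meaningful target effect size for powering the trial". The parent calculation "assumed a loss-to-follow-up rate of 20% with 80 participants remaining in each arm (100 × 0.8"), and on that basis "the parent study is powered to detect moderate or larger effect size difference with > 80% power".
- For this study's own primary outcome, the section concludes: "The current study retains confidence that the sample size will provide adequate power to detect a clinically meaningful effect size for suicide risk".

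Elsewhere, Methods/design says "Recruitment of 160 eligible participants will be conducted independently across the four sites", and the Background also gives the cohort as 160. The inclusion criteria open with "18–55 years of age; DSM-V diagnoses of SZ, schizoaffective disorder, or schizophreniform disorder" and go on to medication stability, medical clearance, capacity and consent to the parent study. Neither the inclusion nor the exclusion criteria require current or past suicidal ideation or behaviour. The only item about risk of harm is an exclusion for homicidal risk. Under Data analyses, efficacy on suicide risk is to be judged by the significance of the time by treatment interaction in a mixed model over 0, 6 and 12 weeks, with two-sided tests at 5%.

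**The concern.** The section declines to calculate power for suicide risk and then asserts the result that such a calculation would have given. The support offered belongs to a different endpoint and a different number of participants.

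The endpoint matters more. The 0.50 SD target was justified by how far people with schizophrenia fall below MCCB averages. That reasoning says nothing about the C-SSRS, and the article gives no C-SSRS effect, SD, baseline distribution or clinically meaningful difference. Because suicidality is not required for entry, some participants will probably have none at baseline. They cannot improve, and their share is not given.

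The number matters too. The parent figure is 80 per arm after losses from 200, while this study states that it recruits 160 in total.

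At stake is the interpretation of the primary result. Efficacy turns on statistical significance, so an unsupported statement of adequate power invites readers to give a non-significant interaction more weight than the design can bear.

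**Working it through.** **Inputs from the protocol article.** Two-sided α of 5% (Data analyses); 1:1 allocation (Randomization); 0.50 SD, 200 enrolled, 20% loss and 80 per arm for the parent trial (Sample size calculations); 160 recruited for this study (Methods/design; Background).

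**Assumption.** The article gives no loss rate for this study, so the parent's 20% is applied to the 160.

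**Formula.** For a two-group comparison of means with n per arm and standardised difference d, power is approximately Φ(d·√(n/2) − 1.960). The smallest d detectable with 80% power is approximately (1.960 + 0.842)·√(2/n). The t-test values quoted below are slightly more exact.

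**1. The parent figure reproduces.**
- Completers: 200 × 0.8 = 160, or 80 per arm.
- Power at d = 0.50: 0.50 × √40 = 3.162; 3.162 − 1.960 = 1.202; Φ(1.202) = 88.5%. The t-test gives 88.2%.
- The parent's statement of more than 80% is therefore right for a 0.50 SD difference in cognition.
- Smallest detectable d: 2.802 × √(2/80) = 0.443; the t-test gives 0.446.

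**2. The same calculation at this study's stated recruitment.**
- Completers: 160 × 0.8 = 128, or 64 per arm.
- Power at d = 0.50: 0.50 × √32 = 2.828; 2.828 − 1.960 = 0.868; Φ(0.868) = 80.7%. The t-test gives 80.1%.
- Smallest detectable d: 2.802 × √(2/64) = 0.495; the t-test gives 0.499.

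**3. Power if the C-SSRS effect is smaller than 0.50 SD.** The article gives no C-SSRS effect, so this is a range and not an estimate (two-sample t-test):

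| Standardised effect | 64 per arm | 80 per arm |
|---|---|---|
| 0.50 | 80.1% | 88.2% |
| 0.40 | 61% | 71% |
| 0.30 | 39% | 47% |
| 0.20 | 20% | 24% |

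The size of the effect that can be achieved on the C-SSRS matters far more than the difference between 64 and 80 per arm.

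**4. What cannot be computed.** The planned test is a time by group interaction over three visits. Its power depends on within-person correlations and variances that the article does not report.

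**The case against.** The strongest reply is that no stated number is wrong. The parent arithmetic reproduces, and with 64 per arm a 0.50 SD effect still has about 80% power. A reader might infer that the lower recruitment by itself destroys the power. It does not: it removes the margin and no more. That part of the reply stands.

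It is also fair that 128 completers is a derived figure. Because 200 × 0.8 happens to equal 160, the 160 may have been carried over from the parent's expected completers. The wording in Methods/design, which speaks of recruiting 160, counts against this, but the article does not settle it.

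A two-sample t-test is not the planned analysis either. The mixed model with multiple imputation includes all randomised participants and uses partial follow-up, so its power may differ from the figures above. This is a real limit on the figures, but it supplies no support for the adequacy claim.

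A reader might go further and put a specific low power on the study by assuming what share of participants start with no suicidality. The documents do not support that. The share is not given, the result depends heavily on what is assumed about the SD, and a participant with none at baseline can still worsen, so fewer emergent cases under exercise would count towards the interaction. The Suicide risk and Suicide risk safety sections do mention recruiting people at higher risk, but no eligibility criterion selects them.

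Finally, a reader might infer that the plan commits itself to treating a null result as proof of no effect. No section states such a rule. The risk lies in how the adequacy sentence will be read.

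None of this supplies a basis for the sentence claiming adequate power.

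**Conclusion.** The claim of adequate power for suicide risk is unsupported. The section itself says that a power analysis was not appropriate, and the only calculation it reports is for cognition. The core fault is carrying a 0.50 SD target from the MCCB composite to the C-SSRS without any C-SSRS effect, SD or baseline distribution, in a sample not selected for suicidality. The mismatch in numbers is secondary.

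On a two-group approximation, and assuming that 160 are recruited and 20% are lost, the study can detect about 0.50 SD with 80% power, against 0.45 SD at the parent's 80 per arm. If the achievable effect is 0.40, 0.30 or 0.20 SD, power at 64 per arm is 61%, 39% or 20%. These figures show how sensitive power is to the effect. They do not show that the study is underpowered, because the true C-SSRS effect and the power of the mixed model are both unknown.

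**What to change.** In Sample size calculations:

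1. Delete the sentence claiming adequate power for suicide risk.
2. State whether 160 means participants recruited or participants completing, and reconcile Methods/design, the Background and this section accordingly.
3. In place of the claim, give the smallest detectable standardised effect at the expected number of completers: about 0.50 SD at 64 per arm if 160 are recruited and 20% are lost, or about 0.45 SD at 80 per arm if 160 are completers. Label it a two-group approximation, and say that power for the C-SSRS is not established.
4. State that the suicide-risk result will be interpreted by its confidence interval, and that a non-significant interaction will not be taken as absence of effect.

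An ordinal model for the C-SSRS and a supportive estimate in participants with baseline suicidality are optional. They belong in the analysis plan, and this point does not depend on them.

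The cost is rewording and a less favourable stated figure. No extra patients are needed.
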